### Trial design

The trial objectives will be investigated using a cross-sectional, unblinded, randomized controlled trial design with two trial arms and a single assessment time point.

### Trial setting

The Medical University of Innsbruck acts as the trial sponsor. The trial will be conducted at six different sites across Europe and Asia: County Hospital of Kufstein (Kufstein, AT), Besançon University Hospital (Besançon, FR), Martin-Luther-University Halle-Wittenberg (Halle, DE), University of Cagliari (Cagliari, IT), General King Hussein Cancer Centre (Amman, JOR), and Kansai Medical University Hospital (Osaka, JP). The trial will recruit inpatients or those attending oncology day care. Patient recruitment is planned for a duration of 27 months.

### Trial participants

To be eligible for inclusion in the trial, patients have to fulfill the following inclusion criteria:
Patients aged 18 or aboveAny cancer diagnosis (no more than 20% per diagnostic group)Current treatment with chemotherapy or immunotherapyInpatient or day clinic settingScoring 3 or above on an initial screening question (“On a scale from 0 to 10, to what degree did you experience physical or emotional symptoms/problems during the last week?”)No psychiatric or mental problems (i.e., no such diagnosis in the medical records)Written informed consent

Participating providers are requested to be either a medical, surgical, or radiation oncologist by training or a specially trained nurse authorized to perform CTCAE assessments in clinical trials, both with at least 1-year experience in oncology.

### Withdrawal

The only criterion for trial dropout is the participant’s wish to do so. This applies to both providers and patients. Withdrawal is possible at any time and does not result in any negative consequences for the former participant.

### Trial procedure

During their day clinic or inpatient stay, all patients provide PRO data by autonomously completing questionnaires (EORTC QLQ-C30 and additional items from the EORTC Item Library) on a tablet PC. Subsequently, after having a medical encounter with the patient, two providers conduct consecutive, independent CTCAE ratings (intervention group: including PRO data, control group: no additional information). All data will be collected on the same day. Figure 1 depicts the trial flow, and Fig. 2 shows the Standard Protocol Items Recommendations for Interventional Trials (SPIRIT) figure [11].

**Fig. 1 Fig1:**
[figure not shown]
Flow chart of the trial procedure

**Fig. 2 Fig2:**
[figure not shown]
Standard Protocol Items: Recommendations for Interventional Trials (SPIRIT) figure

The software Computer-based Health Evaluation System (CHES [12]) is used for electronic PRO questionnaire completion, collection of CTCAE ratings, and completion of electronic CRFs. If it is necessary to assess PROs with paper questionnaires, the questionnaires will be entered into the system right after completion into the trial database to allow in the intervention group electronic result presentation to the provider. Each provider has an individual login, granting access to CTCAE ratings and preventing double ratings by the same provider. Login to the software is possible via any computer or mobile device with an Internet connection. Providers receive the instruction to open the CHES software upfront the patient encounter and to complete the CTCAE rating during the consultation.

Allocation of providers to patient CTCAE ratings does not follow a predefined rule. Providers on duty are requested to complete CTCAE rating on the same day the patient has completed PRO data. If during medical consultations the need for additional treatment or side-effect management becomes apparent, the provider in charge will provide medical advice or referral to other specialists.

### Intervention

In the *control group*, providers use the assessment software to access and complete the CTCAE rating in an electronic format.

In the *intervention group*, providers see the respective patient’s PRO data next to the corresponding CTCAE domain, when accessing the rating. For an example of the CTCAE rating with and without displayed PRO data, see Fig. 3. In addition, providers can access the individual PRO questions and answers. This is especially important for subscales of the EORTC QLQ-C30, which comprise different CTCAE categories (e.g., the questions of the scale EORTC Emotional Functioning include the single CTCAE categories depression, anxiety, and irritability).

**Fig. 3 Fig3:**
[figure not shown]
Presentation of the graphical design of CTCAE ratings and PRO data according to the allocated trial group

Thus, the intervention is the additional provision of PRO data to providers who complete a CTCAE rating for the respective patient. To allow for a naturalistic setting, providers do not receive any special training in CTCAE ratings.

### Randomization and blinding

The PRO assessment software processes a 1:1 randomization to the control or intervention group for each study center. In order to ensure balance between the two groups, minimization is applied when the patient’s basic data is added to the database. For this, a weighted *cutoff* is determined taking the sizes of control and intervention groups into account. Next, a random number between 0.0 and 1.0 is generated. If the random number is smaller than the *cutoff*, the patient is added to the group with less patients. In order to determine *weight*, the randomization procedure has been simulated and *weight* = 0.05 has been determined to produce the desired trade-off between balancing the two groups and preventing predictable group assignments. For each patient, a detailed randomization log is produced, which allows tracing all steps of the randomization procedure.

Providers cannot be blinded in this trial. At the time of PRO assessment, patients do not know whether they are assigned to the study or the control group.

### Assessment instruments

Collection of AE ratings is done for those CTCAE toxicities that are also covered in the EORTC QLQ-C30 and AEs, which are common in patients receiving immunotherapy (peripheral sensory neuropathy, rash, and pruritus).

### Case report form

The case report form for patients contains an eligibility checklist (cancer diagnosis, age at diagnosis above 18 or above, current chemotherapy or immunotherapy, ability to understand the questionnaire cognitively and linguistically, written informed consent provided, no psychiatric or mental problems) and a data sheet for clinical and sociodemographic data (sex, age, country of origin, marital status, living situation, education level, employment status, date of diagnosis, diagnosis, metastasis, disease stage, recurrence, current treatment and treatment intention, concurrent medication, comorbidities, performance status). For patients who discontinue or refuse to participate in the study, the reasons for their decision, sex, age, and diagnosis are documented.

For providers, age, sex, specialty, years of professional experience, previous participation in clinical trials, and research experience (self-reported years of experience) are collected on a separate sheet.

### PRO assessment

Patients complete a total of 46 questions covering 17 adverse events listed in the CTCAE. The EORTC QLQ-C30 by the European Organization for Research and Treatment of Cancer (EORTC) Quality of Life Group [13] was originally developed for use in clinical trials, covers physical and psychosocial aspects, and is one of the most widely used instruments in Europe. It consists of 30 items assessing 5 functioning scales (physical, social, role, emotional, and cognitive functioning), 3 symptom scales (fatigue, pain, and nausea/vomiting), 6 single-item symptoms (appetite loss, dyspnea, diarrhea, constipation, sleeping difficulties, financial difficulties), and a Global Health and Quality of Life scale. In addition, 16 items have been taken from the EORTC Item Library to supplement those CTCAE domains which are covered by one question in the EORTC QLQ-C30 and to include AEs common in chemotherapy and immunotherapy (peripheral sensory neuropathy, rash, and pruritus).

### CTCAE

The NCI has published standardized definitions for AEs, known as the Common Terminology Criteria for Adverse Events (CTCAE), to describe the severity of organ toxicity for patients receiving cancer therapy. The most recent CTCAE version 5.0 was published in November 2017 and became effective in April 2018 [1].

In this trial, providers rate the following 17 CTCAE toxicities: anxiety, depression, irritability, concentration impairment, memory impairment, fatigue, pain, dyspnea, nausea, vomiting, insomnia, anorexia, diarrhea, constipation, peripheral sensory neuropathy, rash, and pruritus.

For the CTCAE ratings, the electronic form includes an info box that shows the exact definitions for each grade as given in the CTCAE version 5.0. Depending on the respective domain, rating from grade I to III or IV is possible. An additional “below grade I” category allows the provider to report that a certain problem is not present (or not qualifying for grade I or above).

### Statistical analysis

Only complete data sets will be used for final analysis. For analysis of the primary trial endpoint, we will compare inter-rater reliability of CTCAE ratings separately for each domain using intra-class correlation (ICC) coefficients. We would like to note that difference in ICC is an unusual endpoint, and to the best of our knowledge, no recommendations are available from the literature what constitutes a minimal important difference in ICC. According to Cicchetti [14], ICCs can be classified as follows: < 0.40 poor, 0.40–0.59 fair, 0.60–0.74 good, and > 0.75 excellent. This is consistent with the classification by Fleiss et al. [15].

For the analysis of the secondary trial endpoints, ICCs will also be compared across AEs to evaluate differences in the reliability of the CTCAE ratings across different types of AEs (e.g., AEs differing in observability). In addition to intra-class correlations, we will also compare percentage of absolute agreement of ratings and percentage for deviations by one and two grades. The frequency of identified AEs (any grade) will be compared between the intervention and control group using Fisher exact tests.

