## Methods

### Trial objectives and endpoints

The trial aims at evaluating the impact of providing PRO data to providers on the accuracy of AE information, assessed by using CTCAE ratings. As there is no gold standard for AE ratings available, accuracy will be investigated in terms of inter-rater reliability.

The primary trial endpoint is the inter-rater reliability of CTCAE provider ratings for 17 AEs in cancer patients with mixed diagnoses. A superiority analysis will compare the inter-rater reliability between the control and the intervention groups for each assessed AE.

There are two secondary trial endpoints: (1) difference in the frequency of identified AEs (any grade) between the intervention and control group and (2) the comparison of the differences in inter-rater reliability between the intervention and control group across the different types of AEs.

The selection of CTCAE toxicities is based on the AEs detected by the European Organization for Research and Treatment of Cancer Quality of Life Core Questionnaire (EORTC QLQ-C30), which cover symptoms normally associated with chemotherapeutic treatments. In addition, AEs associated with immunotherapy have been added as this treatment option is becoming increasingly common in various diagnoses. The following 17 CTCAE toxicities will be assessed in this trial: anxiety, depression, irritability, concentration impairment, memory impairment, fatigue, pain, dyspnea, nausea, vomiting, insomnia, anorexia, diarrhea, constipation, peripheral sensory neuropathy, rash, and pruritus.

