### Power analysis

A sample size of 1024 patients (512 per group) allows to detect differences in ICC with an effect size of *q* = 0.174 (alpha = 0.05, beta = 0.20, two-sided). This effect size corresponds to differences in reliability of, e.g., 0.20 vs 0.36, 0.40 vs 0.54, or 0.60 vs 0.70. Power analysis for ICC has been approximated by Pearson correlation coefficients as suggested by Streiner et al. [16]. The planned sample size is sufficient to detect a difference corresponding to about half a category width in this classification.

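### Fisher exact tests for AE frequency do not fit two correlated ratings per patient: no way of reducing the pair to one yes/no uses both ratings soundly

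*Protocol article*

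**What the plan says.** The section Trial objectives and endpoints of the protocol article defines secondary endpoint (1) as the "difference in the frequency of identified AEs (any grade) between the intervention and control group". Statistical analysis names the test: "The frequency of identified AEs (any grade) will be compared between the intervention and control group using Fisher exact tests". Under Trial procedure, "two providers conduct consecutive, independent CTCAE ratings" for each patient, in both arms. The same section adds, on who rates whom: "Allocation of providers to patient CTCAE ratings does not follow a predefined rule". The article does not say whether the unit of the Fisher test is the rating or the patient, how two discordant ratings become one identified AE, or whether one rater takes precedence.

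Two further facts bear on the choice of method. Centre structures the allocation: "The PRO assessment software processes a 1:1 randomization to the control or intervention group for each study center". And patients in both arms complete the PRO questionnaires before the CTCAE ratings, so a PRO score matching the AE domain is available for everyone.

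**The concern.** Fisher's exact test compares two proportions built from independent yes/no observations, one per unit. This design gives two per patient, and they are correlated. Three routes lead from the pair to a 2×2 table:

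- **Pool all ratings** (1024 per arm). Ratings of the same patient are then treated as independent.
- **Collapse to one result per patient**, counting the AE as present if either rater, or if both raters, recorded it. The frequency then depends on how often the raters agree as well as on how often a provider identifies the AE. Agreement is what the intervention is meant to change.
- **Use one rating per patient.** This is sound but leaves the other rating unused.

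The trial's rationale includes better AE identification. Under the collapsing rules the result could show an apparent change in detection with no change in what providers detect, or hide a real gain, and its direction could depend on the rule chosen.

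**Working it through.** **Inputs.** From the article: 512 patients per arm, two ratings per patient, two-sided alpha 0.05, and the planning reliability pairs 0.20 vs 0.36, 0.40 vs 0.54 and 0.60 vs 0.70 (Power analysis). Assumed, because the article gives none: per-rating AE rates *p* of 10%, 30% and 50%. Also assumed: agreement *k* on any-grade yes/no equals the planning reliability.

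**The plan's own figure.** The sample size concerns the ICC comparison, and the article gives no power for AE frequency. For two independent correlations, n per group = 2 × ((1.960 + 0.842)/0.174)² + 3 ≈ 522, against 512 stated. That is within 2%, so the figure is reproduced.

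**Route 1: all ratings pooled.** The variance of a patient's two-rating total is 2p(1−p)(1+k), while the test assumes 2p(1−p). The true level is therefore about 2 × (1 − Φ(1.96/√(1+k))):

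- k = 0.40: 1.96/√1.4 = 1.656, giving 9.8%
- k = 0.50: 1.96/√1.5 = 1.600, giving 11.0%
- k = 0.70: 1.96/√1.7 = 1.503, giving 13.3%

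Fisher's test is slightly conservative, so simulation at p = 30% gives a little less: about 9%, 10% and 13%. Rates of 10% and 50% give similar results.

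**Route 2: collapsing to one result per patient.** P(both) = p² + k·p(1−p) and P(either) = 2p − P(both). With p = 0.30 in both arms:

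- k = 0.40: both = 0.09 + 0.40 × 0.21 = 0.174; either = 0.60 − 0.174 = 0.426
- k = 0.54: both = 0.09 + 0.54 × 0.21 = 0.203; either = 0.60 − 0.203 = 0.397

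The table shows how often Fisher's test rejects when the per-rating rate is identical in the arms and only agreement differs (20,000 simulated trials per row):

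| Agreement | Rate per rating | Either rater | Rejected | Both raters | Rejected |
|---|---|---|---|---|---|
| 0.20 vs 0.36 | 10% | 17.2% → 15.8% | 8.5% | 2.8% → 4.2% | 18.9% |
| 0.20 vs 0.36 | 30% | 46.8% → 43.4% | 17.4% | 13.2% → 16.6% | 29.7% |
| 0.20 vs 0.36 | 50% | 70.0% → 66.0% | 26.1% | 30.0% → 34.0% | 25.1% |
| 0.40 vs 0.54 | 10% | 15.4% → 14.1% | 7.4% | 4.6% → 5.9% | 11.8% |
| 0.40 vs 0.54 | 30% | 42.6% → 39.7% | 14.7% | 17.4% → 20.3% | 20.0% |
| 0.40 vs 0.54 | 50% | 65.0% → 61.5% | 19.5% | 35.0% → 38.5% | 18.7% |
| 0.60 vs 0.70 | 10% | 13.6% → 12.7% | 6.0% | 6.4% → 7.3% | 6.8% |
| 0.60 vs 0.70 | 30% | 38.4% → 36.3% | 9.4% | 21.6% → 23.7% | 11.3% |
| 0.60 vs 0.70 | 50% | 60.0% → 57.5% | 11.6% | 40.0% → 42.5% | 11.7% |

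With equal agreement in the arms (0.40 vs 0.40), both rules hold their level (3.8% to 4.6%).

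**Route 3: one pre-named rating.** The level is 3.7% to 4.5% in every setting, whatever the agreement.

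**Masking.** Suppose detection truly rises from 30% to 36% per rating while agreement goes from 0.40 to 0.54. Power is about 22% to 24% for either-rater Fisher, 51% for Fisher on one pre-named rating, and about 67% for a patient-clustered comparison of both ratings. With detection unchanged, the clustered comparison stays at about 5%.

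**Ignoring centre.** With one rating per patient and six centres whose AE rates are assumed to run from 25% to 40%, the level of Fisher's test is 4.1%. With rates from 10% to 60% it is 3.0%. There is no inflation.

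**The case against.** The strongest reply is that the article names a test and nothing more. It nowhere says that the ratings will be pooled, Fisher's test is compatible with a patient-level unit, and a condensed article may leave the unit to an analysis plan that is not shown. This stands in part. A reader might infer that the planned analysis has an inflated type I error; the article does not support that, because pooling is only one possible reading. Nor is Fisher's test invalid in itself, since one pre-named rating per patient makes it sound. What survives is narrower. The test is fixed, and no later choice of unit lets it use both ratings without either breaking independence or tying the outcome to agreement.

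A reader might also take the 15% and 20% as false-positive rates. They are not. The either-rater and both-rater frequencies really do differ between arms when agreement differs, and the test detects that difference. The fault is one of interpretation: a change in agreement would be read as a change in detection.

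Two cautions on size also stand. The AE rates are assumed. And the planning reliabilities refer to graded ratings; agreement on any-grade yes/no may be lower. If 0.40 and 0.54 are treated as correlations of underlying normal variables (a strong case of attenuation), yes/no agreement at a 30% rate is about 0.25 and 0.35, and rejection drops to about 9% (either) and 13% (both).

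Finally, a reader might infer that leaving out centre and the PRO score biases the test. It does not. It costs precision only.

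**Conclusion.** The concern holds in this limited form: the named test does not suit two correlated ratings per patient, and each way of applying it has a cost.

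- **Pooling** would roughly double the error or more at agreement 0.40 to 0.70.
- **Collapsing** keeps the level for the collapsed outcome but confounds detection with the primary endpoint, in opposite directions for the two rules. For the pair 0.40 vs 0.54, either-rater rejection is about 7%, 15% and 20% at AE rates of 10%, 30% and 50%, and less if yes/no agreement is below the graded ICC.
- **One pre-named rating** is valid but gives up half the data, and the article names none.

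These sizes rest on the assumed AE rates and on two exchangeable ratings per patient. Dependence between patients rated by the same provider was not modelled. The point concerns one secondary endpoint. It touches neither the sample size nor the primary ICC comparison, but it should be settled before the data are analysed.

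**What to change.** Make the main analysis of secondary endpoint (1) a rating-level comparison that uses both ratings of every patient: a logistic GEE, or a binomial model, with robust standard errors clustered on patient, reported as a risk difference with its confidence interval. Its target, the probability that a provider records the AE, does not move with agreement.

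Include centre and the PRO score matching the AE domain as covariates. They are there for precision and correct no error. The documents do not allow the size of the gain to be stated.

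Keep Fisher's test as a sensitivity analysis on one rating per patient named in advance, for example the first of the two consecutive ratings. Because provider allocation follows no set rule and a provider may rate many patients, add a robustness check that also allows for clustering by provider. For very rare AEs, where the model may fail, fall back on a within-centre permutation test of each patient's mean of the two yes/no ratings.

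The cost is one paragraph in the analysis plan. No new data are needed: both ratings, centre and PRO data are already collected, and each provider's individual login should supply the provider identifier.

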### Power analysis

A sample size of 1024 patients (512 per group) allows to detect differences in ICC with an effect size of *q* = 0.174 (alpha = 0.05, beta = 0.20, two-sided). This effect size corresponds to differences in reliability of, e.g., 0.20 vs 0.36, 0.40 vs 0.54, or 0.60 vs 0.70. Power analysis for ICC has been approximated by Pearson correlation coefficients as suggested by Streiner et al. [16]. The planned sample size is sufficient to detect a difference corresponding to about half a category width in this classification.

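### The half-category sensitivity claim does not match the plan's own examples: the detectable difference is about 60–70% of the fair and good categories, 40% of poor and a quarter of excellent

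*Protocol article*

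**What the plan says.** The Statistical analysis section of the protocol article notes that the literature offers no recommended minimal important difference in ICC, and then adopts a published classification: "< 0.40 poor, 0.40–0.59 fair, 0.60–0.74 good, and > 0.75 excellent". The primary comparison is made separately for each AE.

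The Power analysis section states: "A sample size of 1024 patients (512 per group"), with an effect size q of "0.174 (alpha = 0.05, beta = 0.20, two-sided"). It translates this q into the pairs "0.20 vs 0.36, 0.40 vs 0.54, or 0.60 vs 0.70" and explains the method: "Power analysis for ICC has been approximated by Pearson correlation coefficients". The section closes with the sentence at issue: "The planned sample size is sufficient to detect a difference corresponding to about half a category width in this classification".

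**The concern.** The examples and the closing sentence describe the same detectable difference, yet they disagree for two of the four categories. The pair starting at 0.40 spans 0.14 of a category 0.20 wide. The pair starting at 0.60 spans 0.10 of a category 0.15 wide. Both are about two thirds of a width, not half.

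This matters because the plan concedes that no minimal important ICC difference is available. The closing sentence is the only place where q is tied to a yardstick of meaning. A reader who takes it at face value will believe that, for any AE, the trial has 80% power for a half-category gain. If an AE in the fair or good range then shows no significant difference, that reader would give the result more weight against a half-category gain than the design supports.

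**Working it through.** **Inputs.** From Power analysis: 512 per group, q = 0.174, two-sided alpha 0.05, power 0.80, Pearson (Fisher z) approximation. From Statistical analysis: cut-points 0.40, 0.60 and 0.75. Treating the scale as 0 to 1, the widths are poor 0.40, fair 0.20, good 0.15 and excellent 0.25. Zero as the lower bound of poor is an assumption.

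**Step 1: reproduce the plan's figure.** For two independent correlations, q = atanh(r2) − atanh(r1), with standard error √(2/(n − 3)) = √(2/509) = 0.0627.
- Power at q = 0.174: Φ(0.174/0.0627 − 1.96) = 79.3%.
- n per group for 80% power: 2 × ((1.960 + 0.842)/0.174)² + 3 ≈ 522, against 512 planned (2% apart).
- Examples, from tanh(atanh(r1) + 0.174): 0.20 → 0.360, 0.40 → 0.535, 0.60 → 0.700.

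The sample size, q and the examples are mutually consistent to within rounding.

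**Step 2: express the detectable difference as a share of the category.**

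| Category | Width | Difference | Share |
|---|---|---|---|
| Poor (0.20 vs 0.36) | 0.40 | 0.16 | 40% |
| Fair (0.40 vs 0.54) | 0.20 | 0.14 | 70% (68% with unrounded 0.135) |
| Good (0.60 vs 0.70) | 0.15 | 0.10 | 67% |
| Excellent (from 0.75, to 0.817) | 0.25 | 0.067 | 27% |

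With the bounds exactly as printed (widths 0.19 and 0.14), fair and good become 0.14/0.19 = 74% and 0.10/0.14 = 71%.

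**Step 3: allow for the starting point.** At fixed q the difference shrinks as the starting ICC rises, so the lower edge gives the largest share. The smallest share that still lies wholly inside the category ends at its upper edge:
- Fair: tanh(atanh(0.60) − 0.174) = 0.477; (0.60 − 0.477)/0.20 = 61%.
- Good: tanh(atanh(0.75) − 0.174) = 0.663; (0.75 − 0.663)/0.15 = 58%.

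The within-category range is therefore 61–70% for fair and 58–67% for good.

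**Step 4: power for a true half-category difference**, Φ(q/0.0627 − 1.96).

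| Difference | Position | q | Power |
|---|---|---|---|
| 0.40 vs 0.50 | fair, lower half | 0.126 | 52% |
| 0.50 vs 0.60 | fair, upper half | 0.144 | 63% |
| 0.60 vs 0.675 | good, lower half | 0.127 | about 52% |
| 0.675 vs 0.75 | good, upper half | 0.153 | about 69% |

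For comparison, a half-width in poor has 90% power (0.00 vs 0.20) or 94% power (0.20 vs 0.40), and one in excellent (0.75 vs 0.875) has nearly 100%. There the sentence is conservative.

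**Step 5: what the sentence would require if taken literally.** For 80% power at the plan's own starting points, 0.40 vs 0.50 needs about 998 per group and 0.60 vs 0.675 about 981 per group. That is roughly 1,960 to 2,000 patients in total, against 1,024.

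**The case against.** The best defence is that the sentence is hedged and refers to a category width in the classification as a whole. The four shares in Step 2 average (40 + 70 + 67 + 27)/4 = 51%, and the mean example difference of 0.133 is 53% of the mean width of 0.25. The two-thirds figures also come from the lower edges. A difference starting at 0.59 is 51% of the fair width, and one starting at 0.74 is 46% of the good width. Nothing is concealed either, since n, q, the examples and the cut-points are all printed.

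Part of this stands. Two thirds is the lower-edge value, so the fair description is a range of about 60–70%. But the protocol article states no averaging, and an average over categories from 0.15 to 0.40 wide says little about an AE analysed on its own. The starts near 0.59 and 0.74 give about half only because the difference then lies almost wholly in the next category. Inside fair or good, power for a half-width never reaches 80%.

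Several stronger readings are tempting but not supported:
- **The sample size is wrong.** It is not; it fits the stated q.
- **Half-category gains would usually be missed.** Power of 52–69% means they would be detected somewhat more often than not.
- **Fair and good are the range that will matter.** The Background reports moderate agreement from two cited studies but gives no ICC values, and moderate is not a label in this classification. Where the control-group ICCs will fall is unknown.
- **The shortfall is larger once 17 AEs are allowed for.** The sentence concerns the stated alpha of 0.05 per AE. Any adjustment may be set out in an analysis plan that is not shown, and it has no bearing on whether this sentence is right.

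**Conclusion.** The sentence is wrong as written for the fair and good categories, where the detectable difference is about 60–70% of a width and a half-width has about 52–69% power rather than 80%. It understates the trial's sensitivity for poor (about 40%) and for excellent (about a quarter, from 0.75). The error lies in the interpretation only; design, sample size, q and examples are unaffected.

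The result rests on the plan's own Fisher z approximation, on one unadjusted two-sided 5% test per AE, on complete data for 512 patients per group, and on a 0 to 1 scale for the outer categories. Using the printed category bounds instead of contiguous ones makes the mismatch slightly larger.

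**What to change.** Replace the closing sentence of Power analysis with wording such as: the detectable difference per AE corresponds to about 40% of the poor category, about 60–70% of the fair and good categories, and about a quarter of the excellent category. Leave the sample size, q and the three examples as they are.

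The cost is one sentence. No patients, analyses or procedures change, but the stated sensitivity becomes less favourable in the middle of the scale and more favourable at the two ends.
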